### Outcomes

#### Basic characteristics

The basic characteristics that will be collected are age, (parental) country of birth, religion, educational level, marital status, employment status, and parity.

#### Neonatal health outcomes

The primary neonatal outcomes are perinatal mortality (defined as death per 1000 still- and life births from a GA above 22 weeks to 7 days postpartum) and perinatal morbidity. Perinatal morbidity (composite outcome) is defined as presence of congenital abnormalities, small for gestational age (birth weight below 10^th^ percentile), preterm birth (<37 weeks of GA), Apgar score after 5 min < 7 and/or admission to a neonatal intensive-care unit (immediately after birth). These outcomes will be retrieved from the Perined database, as well as gestational age at birth and birth weight. Other neonatal outcomes that will be addressed in the self-administered questionnaires are child’s crying- and sleeping behavior per 24 h (and to what extent women’s expectations on crying behavior are met), consultations with a general practitioner and/or pediatrician and admission to the hospital within 6 weeks postpartum.

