### Data collection

All women that register for prenatal care at a participating center will receive written information about the study. All women under 24 weeks of gestational age (GA) at inclusion who are able to communicate in Dutch (with assistance) will be asked to participate in the study. Their care provider will verbally inform the women at their first prenatal consultation (generally around 8–12 weeks of GA) and will ask them for informed consent. No exclusion criteria will be employed. Participation includes permission to collect women’s routine pregnancy outcomes as registered in the National Dutch Perinatal Data Registry (Perined, see end of this section) and optional agreement to fill out four self-administered questionnaires. For participants under the age of 18, informed consent of their parents or caregivers will be obtained.

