#### Intervention group

Within the intervention period, pregnant women are offered perinatal care in the CP model. In the CP model traditional prenatal care with one-to-one visits with a perinatal care provider is replaced by the use of a group model [35]. Care is provided by a midwife or an obstetrician (facilitator) and a co-facilitator to groups of eight to twelve women of similar gestational age. Groups meet eight to ten times during pregnancy at the usual scheduled visits, with sessions running for 90 to 120 min. The usual prenatal health assessment is integrated with information, education and peer support. All involved care providers will be trained by licensed trainers to perform CP. The intervention period begins when the center starts to recruit for their first CP group, after the randomized time point. All women included in the study during this period will be part of the intervention group. In addition to the study information, participants will be informed about CP at their first prenatal consultation and will be given the choice to participate in CP. Women that do not participate in CP will receive usual individual care, resulting in two sub-groups within the intervention group. See Fig. 1.

We will use data from the Perined database. The Perined database contains linked and validated routine care information concerning pregnancy, delivery, (re)admissions and pregnancy outcomes [36]. Data are routinely and separately registered by midwives, obstetricians, general practitioners and paediatricians/neonatologists. For this study, the Perined data will be complemented with data from the questionnaires to be completed by participating women at four time points: Table 1 provides an overview of the timing of the different items. Reminders will be sent after 1, 2 and 3 weeks and participants will be reminded by their care provider. Finally, we will use implementation data from CP-group-evaluations and qualitative data from semi-structured interviews with care providers. Outcome measurements are described below. More details on instruments used in the questionnaires are provided in Table 2.

**Table 1 Tab1:** Overview of items in the questionnaires at four measurement time points

T1, inclusion (8–12 weeks of GA)	T2 (28 weeks of GA)	T3 (36 weeks of GA)	T4 (6 weeks postpartum)
Basic characteristics, current weight	Life style Knowledge (2)	Life style (3), medication use (2)	Life style (4), prenatal and perinatal health care use (2)

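### Infant hospital admission to 6 weeks is assigned to optional questionnaires, although the protocol says its registry holds (re)admissions; use the registry for whatever infant period it covers

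*Protocol article*

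**What the plan says.** The Neonatal health outcomes section of the Protocol article divides outcomes by source. Perinatal mortality, the morbidity composite, gestational age and birth weight come from the Perined registry. A second list begins "Other neonatal outcomes that will be addressed in the self-administered questionnaires are" and ends with "consultations with a general practitioner and/or pediatrician and admission to the hospital within 6 weeks postpartum". No registry source is named for the items on that list.

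The two sources differ in reach. Under Data collection, permission to use registry data is part of participation, while the questionnaires rest on "optional agreement to fill out four self-administered questionnaires". Under Intervention group, the article states: "The Perined database contains linked and validated routine care information concerning pregnancy, delivery, (re)admissions and pregnancy outcomes". It adds: "Data are routinely and separately registered by midwives, obstetricians, general practitioners and paediatricians/neonatologists".

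Table 1 has one postpartum questionnaire, at 6 weeks. Against non-response the article plans the following: "Reminders will be sent after 1, 2 and 3 weeks and participants will be reminded by their care provider".

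The registry-based neonatal outcomes have early windows. Mortality runs "from a GA above 22 weeks to 7 days postpartum", and the only admission component of the composite is "admission to a neonatal intensive-care unit (immediately after birth".

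**The concern.** A hospital admission is an event that clinicians record. Here it is assigned to the source that women may decline, although the article describes another source, available for every consenting woman, as holding admission data. The Labor and birth outcomes section handles this differently: registry data come first and the questionnaires complement them.

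Response to a 6-week questionnaire may depend on the event being measured, because a mother whose infant is ill, still in hospital or has died may be less likely to return it. Two consequences follow. The absolute admission rate would be understated. The comparison between periods would also be biased if this dependence differed between control and intervention. Beyond admission to intensive care at birth, this is the only infant hospital-admission outcome that the article names.

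**Working it through.** The plan gives no figure for this outcome, so there is nothing to reproduce. The check has two parts.

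**1. Sources side by side**

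| Feature | Questionnaire | Perined registry |
|---|---|---|
| Named source for infant admission to 6 weeks | Yes | Not named |
| Who is covered | Women who also agree to the questionnaires and respond | All consenting women |
| Recorded by | The mother | Care providers, including paediatricians/neonatologists |
| Said to hold admissions | Yes, to 6 weeks | Yes, as (re)admissions; whose and for how long is not stated |

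**2. What selective response does**

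Inputs, all assumed because the article gives none:
- q: true admission rate.
- rA: response among mothers of admitted infants.
- rN: response among other mothers.

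Observed rate = q·rA / (q·rA + (1 − q)·rN).

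*Absolute rate.* With q = 0.05, rN = 0.70 and rA = 0.50: 0.025 / (0.025 + 0.665) = 0.0362. A true 5% is seen as 3.6%.

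*Same pattern in both periods.* Both observed rates are 0.0362, so a true risk ratio (RR) of 1.00 stays 1.00. If the true RR is 1.5, the intervention rate is 0.075, observed as 0.0375 / (0.0375 + 0.6475) = 0.0547. Then 0.0547 / 0.0362 = 1.51. The comparison is essentially intact.

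*Response raised proportionally in one period.* Take control rA = 0.60 and rN = 0.80, and intervention rA = 0.66 and rN = 0.88. Control gives 0.030 / (0.030 + 0.760) = 0.0380, and intervention gives 0.033 / (0.033 + 0.836) = 0.0380. The RR is 1.00.

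*Pattern in one period only.* Keep rN = 0.70 in both periods.

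| True RR | rA control | rA intervention | Observed RR, q = 0.05 | Range for q = 0.03 to 0.10 |
|---|---|---|---|---|
| 1.00 | 0.70 | 0.50 | 0.72 | 0.72–0.74 |
| 1.00 | 0.50 | 0.70 | 1.38 | 1.36–1.39 |
| 1.50 | 0.70 | 0.50 | 1.09 | 1.09–1.12 |

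*A second set of assumptions.* With q = 0.06 and rN = 0.80 in both periods:
- rA = 0.60 (control) and 0.75 (intervention) give 0.036 / 0.788 = 0.0457 and 0.045 / 0.797 = 0.0565, an RR of 1.24. Swapping the two gives 0.81.
- rA = 0.50 and 0.80 give 0.030 / 0.782 = 0.0384 and 0.048 / 0.800 = 0.0600, an RR of 1.56.

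A difference can therefore be created or hidden, but only if response depends on admission and the ratio rA/rN differs between periods. The 20% loss allowance under Sample size calculation does not inform rA or rN; it is one overall figure, split neither by admission nor by condition.

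**The case against.** The strongest objection is that the article does not show the registry can do the job. It does not say whether (re)admissions means infants or mothers, which wards are included, or how long after birth it runs. The registry windows it does use for infants are short, so a 6-week questionnaire item may have been chosen because the registry stops earlier. The article also describes the two sources as complementary, and a condensed article may leave registry variables and cross-checks to a fuller document. This stands as a limit on the remedy: registry data can be the source only for the infant period they cover. It does not justify leaving the registry unused within that period.

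A second objection is that the mechanism for differential bias is thin. Reminders are planned. Extra contact or extra questionnaire items in the intervention period would plausibly affect response among all mothers, and a proportional change leaves the ratio at 1.00. Women who decline CenteringPregnancy receive usual care. This also stands. Differential selection is possible, for example because reminders come from providers who know the condition, but nothing in the article shows that it will occur.

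A reader might infer that this item is the trial's main later harm signal. The article does not support that: it places the item among other neonatal outcomes, next to crying and sleeping behavior, and calls none of them a harm or safety outcome. A reader might also infer that self-report is the only permitted source. The article names one source but does not rule out a registry check.

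**Conclusion.** The point holds as a low-priority improvement to the data source of a non-primary outcome. Three things are established from the text: the item is assigned to the questionnaires, the questionnaires are optional, and the registry available for all consenting women is said to contain (re)admissions. Lower response among mothers of admitted or deceased infants is a reasonable expectation and would understate absolute rates. Bias in the comparison needs the further assumption that this pattern differs between periods.

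The risk ratios in the working, from 0.72 to 1.56 when there is no true difference, show what the assumed response rates imply and are not forecasts. It would be wrong to read them as evidence that the trial's result for this outcome will be distorted. Mortality and the morbidity composite come from the registry and do not depend on questionnaire response, so the primary neonatal comparison is untouched.

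**What to change.** In Neonatal health outcomes, name Perined as the source of infant hospital (re)admission for all consenting women, over whatever infant period the registry covers, and state that period. Keep the 6-week questionnaire for general practitioner and pediatrician consultations and for admissions after the registry period ends. In women with both sources, report how well they agree.

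The cost is a few more variables in a registry extract that is already planned. If coverage ends before 6 weeks, the registry-based window will be shorter than the one now stated, and admissions after it will still rest on self-report and its possible selection.

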#### Maternal health outcomes

We will collect data on maternal mortality and morbidity (defined as intensive care admission, eclampsia/HELLP, and/or postpartum hemorrhage ≥ 1000 ml), and prenatal and perinatal referrals to specialized obstetrical care.

#### Labor and birth outcomes

Birth outcomes that will be collected are: intended and actual place of delivery, type of delivery (spontaneous or induced), mode of delivery (non-operative vaginal delivery, operative vaginal delivery, and planned and unplanned cesarean section), augmentation (yes/no), and need for analgesia (epidural, remifentanil, pethidine). These outcomes will be retrieved from the Perined database and complemented by data from the questionnaires regarding expectations on labor pain, intentional use of analgesia, perceived duration of delivery (Table 1). We will measure women’s readiness for labor using an item designed by Ickovics et al. [17]. Women’s delivery experience will be measured with the Labor and Delivery Index (LADY-X) [37] and women’s sense of control during delivery with the Labour Agentry Scale (LAS-10) [38].

#### Health behavior outcomes and health literacy

Health behavior outcomes and health literacy will be collected using the questionnaires. Health behavior outcomes are: physical activity (number of 30-min exercise per week and self-judgment physical activity), nutritious behavior (breakfast-, vegetable-, fruit-, juice- and snack-consumption, and self-judgment eating behavior), substance use (tobacco-, alcohol-, and soft or hard drug consumption, and intentions towards smoking cessation), medication use (folic acid use and use of (prescribed) drugs), intention of infant feeding and attitude towards breastfeeding, and infant feeding on day one, at 1 week postpartum and at 6 weeks postpartum. Women’s prenatal and postnatal care knowledge will be measured with a scale developed by Ickovics et al. [17].

#### Psychosocial outcomes

Psychosocial outcomes include perceived stress, coping, social support, and depression. Stress will be measured using the Prenatal Distress Questionnaire (NuPDQ), which is a revised version of the original 12-item scale developed by Yali and Lobel in 1999 [39–41]. Socio-economic and relational stress will be measured by four items of the Cambridge Worry Scale (CWS), complementing the NuPDQ [42–47]. We have added a concluding item on the amount of experienced stress on a scale from 0.0 to 10.0. To measure coping we will use a self-developed short instrument measuring three constructs based on the coping strategies as described by De Ridder & Schreurs (1994), and Savelkoul et al. (2000): problem focused active coping, emotion focused active coping and emotional passive coping [48–50]. Each coping strategy is measured on a subscale and contains three items, which are based on the items of the revised Prenatal Coping Inventory (NuPCI), using the same answering scale (5 point Likert like scale, 0 = never tot 4 = very often) [51]. For example: “How often did you take a walk or performed other physical exercise to feel better?” (emotion focused active coping), “How often did you try not to think about it?” (emotional passive coping), and “How often did you talk to others in the same situation?” (problem focused active coping). Social support will be measured using the social support list-12 Interaction [52, 53]. Depression will be measured using the Edinburgh Postnatal Depression Scale (EPDS) [54].

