Life style and medication use	Life style (2)	Prenatal health care use	Labor experience, and emotions during labor
Preconceptional health care use	Depression	Prenatal Care Knowledge (2)	Breastfeeding initiation and duration
Life style- and Prenatal care Knowledge	Participation and experience of CP^a^	Stress and Coping (2)	Neonatal sleeping- and crying behavior
Stress and Coping		Social Support (2)	Self-efficacy in child care
Social Support		Readiness for Labor and Baby care	Depression (2)
Intended pregnancy education		Expectations on labor and child birth, intentions on infant feeding	Pregnancy education (2)
Intended participation CP^a^		Prenatal Care Satisfaction	Participation CP (3)^a^
		Participation and experience of CP(2)^a^	

^a^Complementary items for intervention group

**Table 2 Tab2:** Overview of instruments that will be used in the study

Tool	Constructs	Items	Scale — Analysis	Validation	References
Labor and birth outcomes					
Readiness for labor-item	On a scale of 0 to 100, where 0 is not at all and 100 is completely, how ready do you feel for labor and delivery?	1 item	0-100 – total score	Not available	Ickovics et al., 2007 [17]
Labor and Delivery Index (LADY-X)	Quality of received care and maternal emotions	7 items: e.g. “Information given by the healthcare professionals during childbirth.”	3 point scale^a^ – sum score (range 0–14)	Test-retest reliability, ICC^b^ > .80; Convergent and divergent validity *r* = .24-.61; Construct validity *p* < .001-.02.	Gärtner et al., 2015 [37]
Shortened Labor Agentry Scale (LAS-10)	Sense of control during childbirth	10 items: e.g.”I felt confident.”	7 point scale (almost always-rarely) – sum score (range 10–70)	A^c^ = .85-.97^d^	Hodnett and Simons-Tropea, 1987 [38] Geerts et al., 2014 [59]
Health literacy					
Prenatal/Postnatal care knowledge	Prenatal and postnatal care knowledge	19 items: e.g.” Babies of mothers who smoke tend to be smaller than babies of mothers who do not smoke.”	5 point scale (definitely false-definitely true) – sum score (range 0–95)	α = .65	Ickovics et al., 2007 [17]
Psychosocial outcomes					

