Revised Prenatal Distress Questionnaire (NuPDQ)	Concerns about birth/baby, concerns about weight/body image, concerns about emotions/relations	9-17^e^ items: e.g. “Are you feeling bothered, worried or upset at this point in your pregnancy about taking care of a new born baby?”	3 point scale (not at all-very much) – sum score (range 0–34)	Test-retest reliability *r* = .75, α = .80-.81^d^	Yali and Lobel, 1999 [39] Yali and Lobel, 2002 [40] Alderlice et al., 2012 [41]
Cambridge Worry Scale (CWS)	Women’s major worries in pregnancy: socio-medical, health, socio-economic, and relational	17 items: e.g. “How much of a worry is your housing to you?”	6 point scale (not a worry-major worry) – at item level or using total (range 0–85) or factor scores	*Socio-medical* α = .71; *Health* α = .70; *Socio-economic* α = .29-.63; *Relational* α = .67. Test-retest reliability *r* = .69-.72	Green and Kafetsios, 1997 [42] Green et al., 2003 [47]
Coping (based on the Revised Prenatal Coping Inventory)	Problem focused active coping, emotion focused active coping, emotional passive coping	9 items: e.g. “How often did you try not to think about it?”	5 point scale (never-very often) – sum score per subscale (range 0–12)	Not available	De Ridder et al., 1996 [48] De Ridder et al., 1998 [49] Savelkoul et al., 2000 [50] Hamilton and Lobel., 2008 [51]
Social Support List-12 Interaction (SSL-12 I)	Daily support, problem support and appreciation support	12 items: e.g. “Do you get invited to a party or dinner sometimes?”	4 point scale (seldom-very often) – scale scores (range 4–16) and sum score (range 12–48)	*Daily support* α = .70-.80^d^; *Problem support* α = .72-.89^d^; *Appreciation support* α = .72-.82^d^.	Kempen et al., 1995 [60] Bridges et al., 2002 [53] Van Sonderen., 2012 [52]
Edinburgh Postnatal Depression Scale (EPDS)	Prenatal and postnatal depression The EPDS was originally developed for postnatal use, but was validated as a prenatal screening instrument.	10 items: e.g. “I have been able to laugh and see the funny side of things.”	4 point scale^a^ – sum score (range 0–30)	α = .80	Cox et al., 1987 [54] Murray et al., 1990 [61] Green et al., 1994 [62] Adouard et al., 2004 [63]
Parenting outcomes					
Readiness for baby care-item	“On a scale of 0 to 100, where 0 is not at all and 100 is completely, how ready do you feel for taking care of your baby?”	1 item	0-100 – total score	Not available	Ickovics et al., 2007 [17]

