## Discussion

Former research has shown a positive effect of CP, including a higher birth weight and more prenatal care satisfaction, however the findings were inconsistent [17, 26, 27, 30, 31]. Furthermore, due to differences in population characteristics and health care system, previous findings cannot be directly extrapolated to the Dutch setting. Our study aims to contribute to the evidence regarding the effect of CP and will give a first indication of the effect and implementation of CP in a Western high-income society other than the USA. Also, by measuring factors that are hypothesized to mediate the effect of CP, we aim to be able to explain the mechanisms that lead to eventual found effects on maternal and neonatal outcomes.

A strength of our study lies in the stepped wedge cluster design. In this design, participating practices are randomly assigned to the period in which they will start providing CP and will function as their own control group before implementing CP. Also, it allows to take into account time effects. Another strength of the study is the use of routine data to assess several neonatal and maternal outcome measures.

One limitation however is the fact that centers are not yet trained in CP and that it takes some time to implement, which may lead to less model fidelity and smaller effect sizes. Fidelity to facilitate group processes in CP and content fidelity are known to associate with significant reductions in preterm birth and intensive utilization of care [58]. To gain more insight in the effects of fidelity of the model as provided by health care providers we will collect data on process and implementation, and will relate it to the effects of CP. The possibility of selection bias by letting women choose between CP or individual care is another limitation of our study. To be able to estimate the degree of selection bias, we will collect numerous demographic and psychosocial data of both groups in the intervention period (CP-participants and Non-CP-participants), also allowing us to correct for differences in basic characteristics. In addition, we will perform an intention-to-treat analysis, as well as a per protocol analysis. Differences in results of both analyses will provide an indication of assumed selection bias.

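### Depression is the only one of the four psychosocial outcomes with no score at inclusion, so its per protocol comparison has no baseline against which to judge self-selection into CP

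*Protocol article*

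**What the plan says.** Under Psychosocial outcomes the Protocol article lists four constructs: perceived stress, coping, social support and depression. For the last it states: "Depression will be measured using the Edinburgh Postnatal Depression Scale (EPDS"). Table 2 describes the EPDS as ten items with a sum score from 0 to 30, and adds: "The EPDS was originally developed for postnatal use, but was validated as a prenatal screening instrument".

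Table 1 fixes when each construct is asked. The first questionnaire is headed "T1, inclusion (8–12 weeks of GA") and the second "T2 (28 weeks of GA"); T3 is at 36 weeks and T4 at 6 weeks postpartum. Depression appears at T2 and, numbered as a second administration, at T4.

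On exposure, the Intervention group section says that women are told about CP and offered the choice at their first prenatal consultation, and that "Groups meet eight to ten times during pregnancy at the usual scheduled visits". Data analysis plans an intention-to-treat comparison of the control group with the whole intervention group, and a per protocol comparison of three subgroups: controls, CP-participants and non-CP-participants. The Discussion accepts that free choice may cause selection bias. To gauge its extent, "we will collect numerous demographic and psychosocial data of both groups in the intervention period", which is also said to allow correction for differences in basic characteristics.

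**The concern.** Within the intervention period women sort themselves into CP or individual care. Depressive symptoms early in pregnancy could plausibly affect both the willingness to join a group and the EPDS score later on. That makes an early EPDS score the most direct variable for judging whether CP-participants and non-CP-participants were alike in depression to begin with. The schedule does not collect one.

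If CP-participants score lower at 28 weeks or postpartum, the reader cannot tell directly whether CP helped or whether women with fewer symptoms chose it. A missed baseline cannot be recovered in the analysis. The 28-week score is no substitute, because it may already carry part of any CP effect.

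**Working it through.** No figure in the protocol bears on this point, so the check is mainly a reading of Table 1 against the text on choice and exposure.

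**Step 1: schedule of the four psychosocial outcomes (Table 1).**

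| Outcome | T1 | T2 | T3 | T4 |
|---|---|---|---|---|
| Stress | yes | – | yes (2) | – |
| Coping | yes | – | yes (2) | – |
| Social support | yes | – | yes (2) | – |
| Depression | – | yes | – | yes (2) |

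The bracketed numbers count administrations. Stress, coping and support carry a 2 at T3 because T1 was the first. Depression carries a 2 at T4, so T2 is its first. The gap is therefore in the schedule itself and is not an artefact of a broken table.

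**Step 2: order of choice, exposure and measurement.** The first consultation is generally at 8–12 weeks (Data collection), and the choice is offered there. At T1 the intervention group is asked about "Intended participation CP"; at T2 the item becomes "Participation and experience of CP". The protocol thus treats T1 as before the sessions and T2 as a time when there is CP experience to report. Eight to ten meetings at the usual visits point the same way. The gestational age of the first session is not given, and women may be included up to 24 weeks, so the amount of CP received by 28 weeks will vary. Depression is measured 0 times before the choice and 2 times after it.

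**Step 3: consequence for each analysis.**

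- *Per protocol, three subgroups.* Observed difference in depression = difference already present at choice + effect of CP. No EPDS value informs the first term directly. Conditioning on the T2 score would condition on something CP may have changed.
- *Intention-to-treat.* The groups are defined by the period of inclusion and not by the woman's choice, so self-selection into CP does not enter. Two things are lost: the precision of a baseline covariate, and a check that women recruited before and after a center starts CP are alike in depression.

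**Step 4: size of the precision loss.** For a baseline score with correlation r to a later EPDS score, adjustment removes a fraction r² of the residual variance. The documents give no r; a range of 0.4 to 0.6 is assumed:

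- r = 0.4: 0.4² = 0.16, or 16%
- r = 0.5: 0.5² = 0.25, or 25%
- r = 0.6: 0.6² = 0.36, or 36%

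These are gains over no adjustment at all. T1 stress, coping and support would already explain some of that variance, so the extra gain from an EPDS baseline would normally be smaller.

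**The case against.** Several counterarguments have force.

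- *The protocol never promises to adjust for depression.* The Discussion uses demographic and psychosocial data to estimate selection bias, and speaks of correction only for basic characteristics, which the section of that name lists as socio-demographic items and parity. This stands. A reader might infer that the protocol plans to correct for selection using depression, or to adjust for the 28-week score; the text supports neither.
- *Selection is not unobserved.* T1 collects a distress questionnaire that covers concerns about emotions and relations, four worry items, an overall stress rating, coping and social support. These can describe psychosocial selection and partly adjust for it. This stands as well. They are proxies, however, and do not measure depressive symptoms.
- *The limitation is already declared.* The Discussion names selection bias and intends to read its extent from the contrast between the two analyses. That contrast gives an indication, but it does not supply the missing starting value.
- *Other secondary outcomes also lack a baseline,* for instance readiness for labor and for baby care, asked at T3 only. That is true, but depression is the one psychosocial outcome treated differently from its three companions, and its instrument is described as valid in pregnancy.
- *T1 is already a long, optional questionnaire.* Ten more items are a real, though small, burden.

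**Conclusion.** The point holds as a weakness in the measurement of one secondary outcome. The schedule gives no depression score before the choice of CP, while the other three psychosocial outcomes each have a T1 value. The per protocol comparison of depression therefore cannot separate a pre-existing difference from a CP effect directly, and the selection-bias plan is weakened for depression.

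Stronger readings are tempting but not supported:

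- A reader might infer that the intention-to-treat result for depression is biased by women's choice. It is not, because that comparison uses the complete intervention group.
- A reader might infer that selection could account for the whole of any observed difference and that the data could never show it. The documents give no basis for sizing the bias, and the T1 proxies offer partial insight.
- A reader might take it as fact that sessions are well under way at 28 weeks. That is a reasonable inference from the T2 item on CP experience, but it is not stated.

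The primary outcomes are untouched. The 16–36% variance figure rests on an assumed correlation and is a gain over no adjustment; the conclusion does not depend on it.

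**What to change.** Add the ten-item EPDS to the T1 questionnaire in both the control and the intervention period. Use that score to describe who chooses CP, to compare case mix between periods, and as the baseline covariate when depression is analysed. Treat the T2 and T4 scores as outcomes only.

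The cost is ten more items in T1, which lengthens an optional questionnaire and may slightly lower its completion. No new instrument is needed.

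If T1 can no longer be changed, state that depression has no baseline, treat the T2 score as an outcome and never as a covariate, and do not interpret the three-subgroup comparison of depression causally. This costs only wording, but it leaves the question of selection open for this outcome.
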